# Background and Significance

## 1.1 Background

Diabetes is a growing global health concern, with its highest prevalence found in low- and middle-income countries and accounts for 1.5 million deaths per year. In Southeast Asia, type 2 diabetes is now the most prevalent disease. (1) According to the International Diabetes Federation (IDF), 34 million people in south-east Asia have diabetes. According to estimates, the number will rise to over 55 million by 2035. (1) In Malaysia, there are approximately 3.9 million people with diabetes, according to the National Health and Morbidity Survey 2019. This rate has increased from 13.4% in 2015 to 18.3% in 2019.

Alternatively, that is approximately one-fifth of the adult population in Malaysia. (2) Moreover, there is a high prevalence of poor glycaemic control with 7.9% mean HbA1c levels. (2) Several studies show that Malaysians with poor glucose control engage in poor self-care practices and have a limited understanding of diabetes. (3-6) Additionally, there are also insufficient diabetes educators to deal with a large number of diabetes patients. (7) Furthermore, COVID-19 has had a significant impact on the entire health care system in recent years. Primary care and hospital practice are currently overburdened with diagnostic testing, monitoring, and management of COVID-19 care, to the point that our routine maintenance for non-communicable diseases can be compromised. (8) Given these factors, there is an urgent need for practical solutions.

Studies have demonstrated that diabetes education improves self-management and glucose control among people with low health literacy. At the same time, clinicians have less time and resources to disseminate information. (9, 10) The number of diabetic education classes is disappointingly low, particularly among the patients with lower socioeconomic classes, those who have not yet developed diabetes complications, and during the COVID19 pandemic when most patients are unwilling to stay in the hospital for longer.

Diabetes self-management programs include health education, a critical component for the management and treatment of chronic diseases. (11) This is the principle that underpins the theory of knowledge, awareness, and practices (KAP) of patients with diabetes are considered the most important factors for assessing health education outcomes. As outlined by the KAP theory, the process of human behaviour change can be divided into three steps: acquiring knowledge, creating attitudes and beliefs, and changing behaviours, during which human health behaviours can also be transformed. (11,12) The use of knowledge can assist patients in making informed decisions about their health when dealing with non-communicable diseases such as diabetes. By empowering them, patients can increase their self-efficacy and improve their self-confidence. Utilising the media in publicity campaigns, creating and creating educational materials, and educating people with diabetes and their families should be part of this effort. (13) Diabetes education and awareness programs will benefit both healthy subjects as prevention measures and help people with diabetes better control their condition. (14,15) It is essential to provide specific and practical guidance for maintaining NCDs’ critical health and community services. National guidance is required to develop and use digital health solutions in NCD care, selfcare, at-home care, and peer support. Yet, with the challenges of the COVID-19 pandemic facing us in the 21st century, it is vital to evaluate how medical information is delivered effectively through health promotion in the practice of new norms. The systematic reviews on using technology to facilitate diabetes self-management reported a significant reduction in glycated haemoglobin and cost-effectiveness. With Internet-delivered diabetes education, many individuals have easier access to the material, and they can take their time with the learning process. (16-18)

## 1.2 Research Question

1. How effective are diabetes education videos in enhancing diabetes knowledge among type 2 diabetes patients?
2. Can diabetes education videos improve clinical outcome among type 2 diabetes patients?

## 1.3 Conceptual Framework

*Figure 1 conceptual framework*

[figure not shown]

# Objective

## General objective

To investigate the effectiveness of web-based education videos that include tailored information on knowledge to educate type 2 diabetes patients in primary care.

## Specific objective

1. To develop web-based education videos for type 2 diabetes patients in primary care.
2. To identify the sociodemographic characteristics (age, gender, ethnicity, education level, marital status, employment status, income, smoking status, history of hospitalisation due to complication of type 2 diabetes) of the type 2 diabetes patient in the primary care clinic among intervention and control groups at baseline.
3. To determine the knowledge scores and clinical outcome (HbA1c, blood pressure, fasting lipid profile, BMI, waist circumference) among intervention and control groups at baseline.
4. To investigate the effectiveness of web-based education videos and compare on the knowledge, diabetes empowerment and clinical outcome (HbA1c, blood pressure, fasting lipid profile, BMI, waist circumference) at baseline, 3months and 6 months between and within the intervention and control groups.

# Methodology

## Study Type and Design

The study design that will be used in this study is a Blocked Randomized Control Trial (RCT) ratio one to one. The samples will be from Klinik Kesihatan Cheras Baru. The study will be conducted and evaluated by the requirement in the Consolidated Standards of Reporting Trials (CONSORT) Statement. (19)

## Study Population

The study population consists of type 2 diabetes patients through walk-in and follow-up clinic registrations in the primary care clinics from 1^st^ June 2024 to 31th December 2024.

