## Study Duration and Timeline

The duration of data collection of the research is 6 months, from 1^st^ June 2024 to 31^th^ December 2024.

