## Data collection method

Data will be collected by the research by selecting type 2 diabetes patients from the baseline. These type 2 diabetes patients will have to meet the inclusion and exclusion criteria, once it is fulfilled the type 2 diabetes patients will be recruited. A research assistant will approach patients on the day of their follow-up visit at Klinik Kesihatan Cheras Baru. As part of the consent process, the investigator will explain and provide the Patient Information Sheet to the participant and an agreement to receive calls and messages from the researcher for research purposes. They will keep their phone numbers private and will only be contacted or messaged every four weeks to remind them to complete the videos watching and follow-up appointment. The patients will, however, be given one week to consider their participation if they are still deciding on the recruitment day. We will conduct a one-to-one ratio randomization control trial with the control and intervention groups.

During the same day, all participants will be given a hard copy self-administered questionnaire by research assistance to complete and their latest clinical profile (height, weight, BMI, waist circumference, blood pressure, latest blood test for HbA1c and fasting lipid profiles) will be taken from their medical records. The self-administered questionnaire will take about 20minutes to complete. This stage will be considered as baseline assessment for both control and intervention groups. After the questionnaire, both groups will continue their follow up in the clinic like usual. The intervention group will take place after all the participants complete the questionnaire. The participants will be told about the structure of the program. There will be a research assistant who the researcher has already trained to assist and teach the participants how to assess and use the web-based online education videos. They will need to watch all the videos. The research assistant will follow up with their progress and remind them to complete the video in every four weeks via phone call.

After three months of the intervention on the first week of September (2/9/2024 to 6/9/2024), both of the intervention and control group participants will return to the clinics for follow up. During the follow-up, participants will be given a self-administered questionnaire to answer.

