At six months’ time point from the baseline on the last week of December (23/12/2024 to 31/12/2024), both of the intervention and control group participants will return to the clinics for follow up. During the follow-up, participants will be given a self-administered questionnaire to answer and their latest clinical profile (height, weight, BMI, waist circumference, blood pressure, latest blood test for HbA1c and fasting lipid profiles) will be taken from their medical records. This is a basic diabetes education video for self-care and education, and no further treatment will be given after the study has been completed. You will continue your diabetes follow up as usual.

*Figure 2: Flow of the process*

[figure not shown]

Collection of questionnaires port write up and dissemination of result

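### The registration period, the data-collection period and the two fixed follow-up weeks cannot all hold, so elapsed time at the 3- and 6-month visits is not what the labels say

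*Protocol*

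**What the plan says.** - **Protocol 3.2 (Study Population)** defines the population through "walk-in and follow-up clinic registrations in the primary care clinics from 1^st^ June 2024 to 31th December 2024".
- **Protocol 3.8 (Study Duration and Timeline)** repeats those dates for the whole study: "The duration of data collection of the research is 6 months, from 1^st^ June 2024 to 31^th^ December 2024".
- **Protocol 3.9 (Data collection method)** describes individual recruitment: "A research assistant will approach patients on the day of their follow-up visit at Klinik Kesihatan Cheras Baru". Baseline follows at once: "During the same day, all participants will be given a hard copy self-administered questionnaire by research assistance to complete". Undecided patients may take one more week.
- **The same section** fixes the follow-up visits by calendar for both groups. The first is "After three months of the intervention on the first week of September (2/9/2024 to 6/9/2024"). The second is the "six months’ time point from the baseline on the last week of December (23/12/2024 to 31/12/2024").
- **The table in 3.20 (Study Outcome)** repeats both date ranges. The questionnaire is given at all three time points; the clinical profile is taken only at baseline and in December.
- **On when the videos begin,** 3.9 says: "The intervention group will take place after all the participants complete the questionnaire".

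The protocol gives no separate enrolment close date, no tolerance around either visit, and no follow-up after 31 December 2024.

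**The concern.** Recruitment at each patient's own clinic visit gives each participant a different baseline date. A follow-up visit fixed to one calendar week then falls at a different elapsed time for each of them. Objective 4 in section 2.2 compares the groups at baseline, 3 months and 6 months, and 3.12 plans a paired test at 6 months and a GEE. All of these rely on the visit labels as the time axis.

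How much is at stake depends on when enrolment closes, which the protocol does not say.

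- **If enrolment is open to 31 December,** many participants would have no 3-month visit at all. Late enrolees would also supply a nominal 6-month outcome after little or no exposure, which pulls the estimated 6-month effect towards zero. Because HbA1c and lipids are the most recent values in the record, a late enrolee's December value could even be the baseline test.
- **If enrolment is confined to June,** the loss is smaller: visit times that vary by about a month around labels that no enrolment date meets exactly.

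**Working it through.** **Inputs (Protocol 3.2, 3.6, 3.8, 3.9, 3.20).** Registration and data collection 1 June to 31 December 2024; nominal 3-month window 2-6 September; nominal 6-month window 23-31 December; 232 participants. The sample size is not in question: (2.21² + 2.33²) × (1.96 + 0.8416)² / 1.0² = 80.9, so 81 per group, and 81 / 0.70 = 115.7, so 116 per group and 232 in total, as stated.

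**Step 1. The stated duration.** From 1 June to 31 December is 30 + 31 + 31 + 30 + 31 + 30 + 31 = 214 days inclusive. The first and last dates are 213 days apart, and 213 / 30.44 = 7.0 months. The stated 6 months does not match its own dates.

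**Step 2. Distance between the two visit windows.** 6 September to 23 December is 108 days; 2 September to 31 December is 120 days. That is 3.5 to 3.9 months. Exact visits at three and six months from one baseline would be about 91 days apart here (30 + 31 + 30). The windows are therefore at least 108 − 91 = 17 days too far apart, whenever enrolment closes.

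**Step 3. Which baseline dates fit.**

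| Tolerance on each visit | Fits 3 months | Fits 6 months | Fits both |
| --- | --- | --- | --- |
| none (as written) | 2-6 June | 23-30 June | none |
| ±9 days | 1-15 June | 14 June-9 July | 14-15 June |
| ±14 days | 1-20 June | 9 June-14 July | 9-20 June (12 days) |

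**Step 4. Scenario A: enrolment open to 31 December.** The protocol gives no accrual rate. Even accrual over the 214 days is assumed here.

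- Enrolled after 6 September: 24 + 31 + 30 + 31 = 116 days; 116 / 214 = 54%, or about 126 of 232.
- At least three months by 6 September: 6 days by calendar months or 7 days by a 91-day count; 6 / 214 to 7 / 214 = about 3%.
- At least six months by 31 December: 30 days by calendar months or 32 days by a 182-day count; 30 / 214 = 14% to 32 / 214 = 15%, or about 33 to 35 of 232.

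Accrual weighted towards June would make the problem smaller; accrual weighted towards the end would make it larger.

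**Step 5. Scenario B: enrolment confined to June.**

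- Nominal 3-month visit: 64 days (30 June to 2 September) to 97 days (1 June to 6 September).
- Nominal 6-month visit: 176 days (30 June to 23 December) to 213 days (1 June to 31 December).
- Accrual needed: 232 / 30 = 7.7 participants per calendar day at one clinic, all with HbA1c above 8% and one per household. The protocol states neither this constraint nor a June close.

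**The case against.** The best defence is that 3.2 never uses the word enrolment. It describes a source population, and its dates match those in 3.8, so it may simply restate the study period. Section 3.9 places the September week three months into the intervention and the December week six months from baseline, and both point to recruitment around June. On that reading both arms attend in the same weeks and allocation is randomised 1:1. The spread in elapsed time is then shared between arms in expectation and does not bias the between-group comparison. The September visit collects only the questionnaire, so the clinical outcomes do not depend on that window. This part of the defence stands.

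It also rules out some stronger readings that a reader might infer:

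- **That most participants cannot have a 3- or 6-month outcome.** This needs both the enrolment reading of 3.2 and even accrual. The first is plausible but not certain; the second is not in the document.
- **That no enrolment date can serve both visits.** This is true only with zero tolerance. Within two weeks of each visit, 9 to 20 June works.
- **That exposure is detached from baseline because the videos wait for the whole cohort.** The sentence on when the intervention starts can equally mean after each participant's own questionnaire on the day. A cohort-wide start would also require enrolment to close first, which does not fit enrolment to 31 December.

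The defence does not remove the conflict. No June close is written anywhere, individual recruitment is, the duration in 3.8 is wrong by its own dates, and the visit windows are too far apart under either reading.

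**Conclusion.** The concern holds as an inconsistency among 3.2, 3.8, 3.9 and 3.20, with a consequence that depends on an enrolment close date the protocol does not give.

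- **Independent of any assumption:** the 6 months in 3.8 is 7 by its dates; the two visit windows are 108-120 days apart; and no baseline date gives exactly three and six months.
- **If enrolment runs to 31 December, with even accrual assumed:** about 54% miss the September visit by design, and about 14-15% can reach six months. There is structural missingness at 3 months, and the nominal 6-month effect is diluted if benefit needs exposure time.
- **If enrolment is confined to June:** visits fall at 64-97 and 176-213 days. The cost is imprecise labelling of time, without bias in the randomised comparison.

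A reader might conclude that the trial cannot answer its 3- and 6-month question at all. The document does not support that, because under June enrolment the comparison remains valid at roughly those times. An analysis plan could define windows, but it could not supply a visit that was never scheduled, so the correction belongs in the protocol.

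**What to change.** Amend 3.2, 3.8, 3.9 and the table in 3.20 together:

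1. State an enrolment close date, separate from the end of data collection.
2. Replace the fixed September and December weeks with assessments at 3 and 6 months from each participant's own baseline or randomisation date, with a stated window (for example ±2 weeks).
3. End data collection no earlier than six months after the last enrolment, allowing for the window.
4. Correct the duration in 3.8 so that it matches its dates.
5. Clarify whether the intervention starts after each participant's own questionnaire or after the whole cohort's, and reconcile this with the description of the September visit.

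**Cost.** Follow-up visits would spread over more weeks, and the last visit may be later. Keeping 31 December as the end means closing enrolment by about 30 June, at roughly 8 participants per calendar day, whose feasibility the protocol does not address. Keeping enrolment open to 31 December means follow-up to about 30 June 2025. Neither choice adds patients or procedures, and the sample size of 232 is unaffected.

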## Inclusion Criteria

Those eligible for enrolling are type 2 diabetes patients aged 18 years or older, who have been diagnosed and followed up for type 2 diabetes for at least six months, have an HbA1c greater than 8% at the time of enrolment, and only one family member from each household will participate in the study. Furthermore, they should be able to understand Malay and have internet access at home.

## Exclusion Criteria

Exclusion criteria include patients who are acutely ill, have psychiatric illness, who are bedridden and rely on nursing care to perform daily activities and who are intellectually disabled, as determined by a community-centred board.

## Withdrawal Criteria

Patients whom who wish to withdraw from the study can withdraw from the study anytime by informing principal investigator.

## Sample Size

Sample size was calculated based on two mean groups formula (20) , mean±sd of knowledge differences for intervention group and control group were 0.7±2.21 and -0.30±2.33 (16), 80% of power, 5% of risk error, 30% attrition rate, the sample size needed per group is 116 (total is 232).

## Recruitment and randomisation

The study design that will be used in this study is a Blocked Randomized Control Trial (RCT) ratio one to one.

## Study Duration and Timeline

The duration of data collection of the research is 6 months, from 1^st^ June 2024 to 31^th^ December 2024.

## Data collection method

Data will be collected by the research by selecting type 2 diabetes patients from the baseline. These type 2 diabetes patients will have to meet the inclusion and exclusion criteria, once it is fulfilled the type 2 diabetes patients will be recruited. A research assistant will approach patients on the day of their follow-up visit at Klinik Kesihatan Cheras Baru. As part of the consent process, the investigator will explain and provide the Patient Information Sheet to the participant and an agreement to receive calls and messages from the researcher for research purposes. They will keep their phone numbers private and will only be contacted or messaged every four weeks to remind them to complete the videos watching and follow-up appointment. The patients will, however, be given one week to consider their participation if they are still deciding on the recruitment day. We will conduct a one-to-one ratio randomization control trial with the control and intervention groups.

During the same day, all participants will be given a hard copy self-administered questionnaire by research assistance to complete and their latest clinical profile (height, weight, BMI, waist circumference, blood pressure, latest blood test for HbA1c and fasting lipid profiles) will be taken from their medical records. The self-administered questionnaire will take about 20minutes to complete. This stage will be considered as baseline assessment for both control and intervention groups. After the questionnaire, both groups will continue their follow up in the clinic like usual. The intervention group will take place after all the participants complete the questionnaire. The participants will be told about the structure of the program. There will be a research assistant who the researcher has already trained to assist and teach the participants how to assess and use the web-based online education videos. They will need to watch all the videos. The research assistant will follow up with their progress and remind them to complete the video in every four weeks via phone call.

After three months of the intervention on the first week of September (2/9/2024 to 6/9/2024), both of the intervention and control group participants will return to the clinics for follow up. During the follow-up, participants will be given a self-administered questionnaire to answer.

At six months’ time point from the baseline on the last week of December (23/12/2024 to 31/12/2024), both of the intervention and control group participants will return to the clinics for follow up. During the follow-up, participants will be given a self-administered questionnaire to answer and their latest clinical profile (height, weight, BMI, waist circumference, blood pressure, latest blood test for HbA1c and fasting lipid profiles) will be taken from their medical records. This is a basic diabetes education video for self-care and education, and no further treatment will be given after the study has been completed. You will continue your diabetes follow up as usual.

*Figure 2: Flow of the process*

[figure not shown]

Collection of questionnaires port write up and dissemination of result

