#### Independent Variables

Independent variable will be the web-based education video for the intervention group and a talk about diabetes educations for the control group

Intention to treat (ITT) method will be used for statistical analysis. Statistical analysis will be done using IBM SPSS Statistics version 27. Descriptive analysis will be conducted to check the error and distribution of data. Histogram with normal curve will be used for normality checking. Independent-t test will be used to investigate the difference of diabetes knowledge test between group. Paired t test will be used pretest and post-test after 6 months. Generalized Estimating Equation (GEE) will be used to investigate the effectiveness of diabetes knowledge and clinical outcome, adjusted with covariates. P<0.05 will be considered statistically significant.

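### Support calls and video teaching are described only for the intervention arm while the objectives name the videos alone, and the four-weekly appointment reminder is not assigned to an arm

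*Protocol*

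**What the plan says.** Protocol 3.9 (Data collection method) first describes consent. Participants give "an agreement to receive calls and messages from the researcher for research purposes", and they "will only be contacted or messaged every four weeks to remind them to complete the videos watching and follow-up appointment". This text comes before the sentence on randomisation and names no arm.

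After the baseline questionnaire, "After the questionnaire, both groups will continue their follow up in the clinic like usual". The text then turns to the intervention group. A trained research assistant is "to assist and teach the participants how to assess and use the web-based online education videos", and "The research assistant will follow up with their progress and remind them to complete the video in every four weeks via phone call". No equivalent teaching or call is described for controls. Both arms are to return at three and six months.

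The only control activity named elsewhere is in 3.12 (Independent Variables): "a talk about diabetes educations for the control group". Section 3.9 does not mention this talk, and neither section describes it as recurring contact.

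The purpose is stated in terms of the videos only. The general objective (2.1) begins "To investigate the effectiveness of web-based education videos that include tailored information on knowledge". Both research questions (1.2) and specific objective 4 (2.2) likewise name only the videos. Section 3.13 mentions the possibility of using the videos in all primary care clinics, without mentioning calls.

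**The concern.** There are two linked problems.

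**What the result will be about.** The intervention arm receives videos, help in using them and a periodic progress call. A difference between arms reflects all three, while the conclusion as framed would credit the videos. This matters for the trial's own rationale. Section 1.1 argues from a shortage of diabetes educators and limited clinician time, and 3.13 looks ahead to wider use. A clinic that adopts the videos without the calls would be relying on something the trial did not test. Empowerment, which 3.20 lists as a primary outcome, is measured by self-administered questionnaire and could plausibly respond to personal attention.

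**Who is reminded to attend.** The consent text puts the video prompt and the appointment reminder into one contact and does not say who receives it. If attendance prompting differs by arm, loss to follow-up may differ by arm too, and the participants who return may no longer be comparable.

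**Working it through.** **1. Reproduce the plan's figure.** Inputs from 3.6: mean changes 0.7 and -0.30, so the difference is 1.0; SDs 2.21 and 2.33; power 80%; 5% error, taken as two-sided; attrition 30%.

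- Pooled SD = √[(2.21² + 2.33²)/2] = 2.271.
- n per group = 2 × [2.271 × (1.960 + 0.842)]² / 1.0² = 80.9, rounded up to 81.
- With attrition: 81 / (1 - 0.30) = 115.7, rounded up to 116.

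The stated 116 per group is reproduced. The point does not depend on it, and no change in sample size follows.

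**2. Compare the arms as described.**

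| Element | Intervention | Control |
|---|---|---|
| Videos | Yes | No |
| Teaching on using the videos (3.9) | Yes | Not described |
| Four-weekly progress call (3.9) | Yes | Not described |
| Usual clinic follow-up (3.9) | Yes | Yes |
| Education talk (3.12) | Not described | Named, not detailed |
| Four-weekly appointment reminder (3.9, consent text) | Arm not named | Arm not named |

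The arms differ in staff contact as well as in videos, and no third arm or other design feature separates the two.

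**3. Scale of the contact.** Section 3.10 lists 10 topics at about 3 minutes per video: 10 × 3 = 30 minutes. One call every four weeks over about 26 weeks gives 26/4 = 6.5, so about 6 calls per participant and 116 × 6 = 696 in the arm. This is an upper bound, because 3.9 gives the interval but not when the calls stop.

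**4. Illustration: part of the effect comes from contact.** The shares below are assumptions; the protocol gives none. With 81 per group, the standard error is 2.271 × √(2/81) = 0.357, and power = Φ(effect/0.357 - 1.960).

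| Share of the 1.0-point difference due to contact | Video part | Power for the video part alone |
|---|---|---|
| 0% | 1.00 | 80% |
| 10% | 0.90 | 71% |
| 25% | 0.75 | 56% |
| 50% | 0.50 | 29% |

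**5. Illustration: unequal loss, 30% overall.** These splits are also assumptions.

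| Loss, intervention / control | Evaluable | Power |
|---|---|---|
| 30% / 30% | 81.2 / 81.2 | 80% |
| 20% / 40% | 92.8 / 69.6 | 79% |
| 15% / 45% | 98.6 / 63.8 | 78% |

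Power hardly moves. Unequal attendance would do its harm through bias, which the documents give no means to size.

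**6. The two readings of the consent text.** If the combined contact goes to the intervention arm only, controls get no described appointment prompt. If it goes to everyone as worded, controls are reminded to complete videos they were not allocated. Neither reading is satisfactory.

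**The case against.** Prompting people to use a web programme is an ordinary part of delivering it, and 3.9 describes it openly. For knowledge, the outcome behind the sample size, a reminder would act mainly by increasing viewing, which is adherence and not a rival explanation. Full matching of contact is a choice between an explanatory and a pragmatic design. The calls may stop once the videos have been watched. Section 3.13 speaks only of a potential for wider use. The flow chart in 3.9 is not shown in the text at hand and may show contact by arm.

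Much of this stands, and it rules out several stronger readings that a reader might infer:

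- **Individual coaching in one arm.** The documents describe teaching participants to access and use the videos. The one-to-one wording in 3.9 is the allocation ratio, and no discussion of diabetes during the calls is described.
- **A difference that could not be credited to the intervention at all.** Randomisation still supports the comparison of the package with the comparator. Only the split between videos and support is lost.
- **Unequal attendance support as a fact, or a retention gap of a given size.** The progress call concerns the videos only, and the sole appointment reminder names no arm. It is a risk that the wording leaves open.

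The objection does not close the gap between what is delivered and what is claimed. Even if calls work only by increasing viewing, videos offered without calls may be watched less and so do less.

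**Conclusion.** The point holds in a limited form. As written, the trial can estimate the effect of web-based videos with assistant teaching and four-weekly reminder calls, but its objectives would have it conclude on the videos alone. Separately, 3.9 leaves open who receives the appointment reminder, and both possible readings cause a difficulty.

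The size cannot be calculated from the documents. The power figures for a contact share and the splits of attrition are illustrations on assumed values, and the count of about 6 calls is an upper bound. The sample size calculation is sound and is not affected. The conclusion assumes that the figure not shown does not assign matching contact to controls. The change is worth making because it costs little and makes the conclusion match what was tested. The separate disagreement between 3.9 and 3.12 on whether controls receive a talk also needs reconciling, but this point does not depend on how it is settled.

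**What to change.** - **In 3.9, assign the contact by arm.** Send the identical appointment reminder, by the same channel and on the same schedule, to both arms. Restrict the video-completion prompt to the intervention arm, and change the consent text to match.
- **If the progress calls are kept, name them.** In 2.1, in 2.2 (objective 4) and in the statement on wider use in 3.13, define the intervention as *web-based videos with four-weekly telephone reminders*. State in 3.9 when the calls stop.

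The cost is routine messages to about 116 controls, for which the agreement to calls and messages already appears in the consent process, and a slightly narrower claim. The sample size does not change. If recruitment has already taken place, the reminder change is no longer possible, but the package can still be named in the report, together with who was contacted and the attendance by arm.
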